## Abstract

**Background:**

Measuring the quality of provided healthcare presents many challenges, especially in the context of medical rehabilitation. Rehabilitation is based on a holistic biopsychosocial model of health that includes a person’s long-term functioning; hence, outcome domains are very diverse. In Germany, rehabilitation outcomes are currently assessed via patient and physician surveys. Health insurance claims data has the potential to simplify current quality assurance procedures in Germany, since its comprehensive collection is federally mandated from every healthcare provider. By using a cross-sectoral approach, quality assessments in rehabilitation can be adjusted for the quality provided in previous sectors and individual patient risk factors.

**Methods:**

SEQUAR combines two studies: In a prospective longitudinal study, 600 orthopedic rehabilitation patients and their physicians are surveyed at 4 and 2 time points, respectively, throughout rehabilitation and a follow-up period of 6 months. The questionnaires include validated instruments used in the current best-practice quality assurance procedures. In a retrospective cohort study, a nationwide claims database with more than 312,000 orthopedic rehabilitation patients will be used to perform exploratory analysis for the identification of quality indicators. The identified SEQUAR claims data quality indicators will be calculated for our prospective study participants and tested for their ability to approximate or replace the currently used, best-practice quality indicators based on primary data.

**Discussion:**

The identified SEQUAR quality indicators will be used to draft a novel, state-of-the-art quality assurance procedure that reduces the administrative burden of current procedures. Further research into the applicability to other indications of rehabilitation is required.

**Trial registration:**

WHO UTN: U1111-1276-7141; DRKS-ID: DRKS00028747 (Date of Registration in DRKS: 2022/08/10).

**Supplementary Information:**

The online version contains supplementary material available at 10.1186/s12913-023-10074-w.

## Background

Roughly 100,000 avoidable deaths per year in US hospitals occur due to medical error—that is the imposing figure the Institute of Medicine reported in 2000 [1]. The very influential report, aptly titled “To Err is Human”, has been credited as a turning point for patient safety and quality control in healthcare [2, 3]. In Germany, efforts to implement systems of quality control in healthcare (also known as quality assurance) are considerably older—lawmakers codified federal mandates to monitor, assess, and improve the quality of care in hospitals, doctor’s offices and other medical facilities in 1988 via internal management systems and external assessment procedures [4]. However, measuring the quality or comprehensive, long-term outcomes of medical care was (and still is) not an easy feat. Patient surveys have to be conducted and processed, medical records examined and coded, charts reviewed and abstracted.

### Quality assurance with claims and administrative data

To mitigate the efforts of primary data collection, researchers have been tapping into the potential of administrative or health insurance claims data. This (often billing) data is routinely collected, readily available, and has been successfully used in a variety of healthcare and public health research: Estimating disease-specific cost to a healthcare system [5], comparing healthcare costs across different countries [6], or tracking opioid use in a population over time [7], to name a few examples.

Some countries use administrative and claims data to publish nationwide, comprehensive quality of care ratings for their hospitals or even individual doctors (e.g., “Hospital Compare” in the US, or the Care Quality Commission’s website in the UK). In others, administrative and claims data has been used to develop quality indicators, which are standardized measures that quantify the rather abstract concept of care quality in numbers (e.g., staffing ratios, post-op mortality rates, average wait times; [8]). Quality indicators can be disease-specific, like Japan’s nationwide quality of cancer care quality indicators [9]), or a general assessment of hospital quality, like AHRQI™ in the US (Agency for Healthcare Research and Quality Indicators; [10]) and QSR in Germany (Quality Assurance with Routine/Claims Data, German: Qualitätssicherung mit Routinedaten; [11]). Claims data has also been used to assess the proportion of patients participating in cardiac rehabilitation after a heart attack [12], approximate the quality of care in rehabilitation facilities after knee replacement [13], and evaluate the effect of orthopedic rehabilitation after hip fractures on hospital readmission [14].

### Quality of care in medical rehabilitation

Measuring quality of care and long-term outcomes of medical rehabilitation tends to be particularly difficult because outcome domains are so diverse. Medical rehabilitation and its intended outcomes are based on the biopsychosocial model of WHO’s Classification of Functioning, Disability and Health (ICF): Illness, health, and a person’s function are a result of a complex interaction between the person and their environment, influenced by biological factors (like physical health), psychological factors (like coping skills), and social factors (like support networks; [15]). Intended outcomes include restoring function and well-being in many areas of a patient’s life, such as a return to regular daily activities, family life, and the workforce [16].

In much of the world, medical rehabilitation is provided in outpatient centers, part time, with limited therapies during evening or weekend hours [17]. Germany (like Austria and Switzerland), however, administer medical rehabilitation mostly in inpatient rehabilitation facilities (IRFs). These IRFs can be traced back to a century’s old tradition of “treating” a wide range of diseases in health resorts and sanatoriums with natural and holistic remedies such as fresh air, water treading, and thermal baths [18, 19]. Today, the average patient completes German inpatient rehabilitation in 25 days [20] and receives therapies and trainings that target all domains of life in accordance with the ICF model. Medical rehabilitation is an integral part of the German healthcare system—in 2019^1^, the biggest German insurance fund DRV spent roughly 7.5 billion US Dollars on medical rehabilitation [21].

### Rehabilitation quality assurance in Germany

These intricacies of German medical rehabilitation make external procedures of quality assurance in IRFs a very elaborate process. One of the two widely used existing procedures, QS-Reha® (Quality Assurance in Rehabilitation®), requires patients and physicians to participate in an empirical survey [22, 23]. Take rehabilitation for musculoskeletal indications, for example: Patients are to complete two questionnaires distributed to them by the IRF at two set time points, while doctors submit one report form. That amounts to 35 pages of primary data per patient that have to be collected and submitted to the evaluating party, who has to process and record them into databases. Conservatively, 55,000 musculoskeletal rehabilitation patients participated in the last wave of evaluations, which means that 2 million pages of primary data had to be handled [23]. This places an enormous amount of administrative burden on IRFs that are already struggling with understaffing [20, 24].

Because Germany’s healthcare system is predicated on (mandatory) statutory health insurance (SHI), available claims data is very comprehensive. Aside from personal data (names, addresses, dates of birth), German SHIs record billing and diagnostic data on inpatient stays; outpatient treatment; pharmacological treatment; physical, occupational and speech therapy; medical aids like walkers, hearing aids, and prescription glasses; and any additional nursing care or nursing services received in-home. The collection and transfer of this data from medical providers to SHIs is mandated by the German Social Code (e.g., parts of Book V and X), which also allows for processing of claims data for research purposes [25]. It seems that German claims data would be uniquely suited to employ in procedures of quality assurance, yet we know very little about its potential in the context of medical rehabilitation.

Additionally, there is very limited research examining the impact of quality of care received in a previous sector (e.g., an operating hospital before follow-up rehabilitation) on the quality and long-term outcomes of rehabilitation, even though many researchers (and lawmakers) have identified the need for German healthcare research to coordinate across sectors [20, 26, 27]. It does stand to reason that the treatment outcome of orthopedic rehabilitation after joint replacement hinges on the success of the previously performed surgery—patients that received surgery and postoperative care in a high-quality hospital are likely in better health at the start of follow-up rehabilitation (baseline). Thus, adjusting for risks in previous sectors (e.g., hospital quality, perioperative complications, pre-existing conditions) could likely improve the accuracy of quality assessment in subsequent sectors.

### Research aims

In SEQUAR (Cross-**Se**ctoral **Qu**ality **A**ssurance With **R**outine/Claims Data), we will close the gap in research by utilizing cross-sectoral claims data from a major German SHI, AOK. We will evaluate its potential to simplify current quality assurance procedures in medical rehabilitation and improve risk adjustment modelling, which accounts for individual patient risk factors when determining a facility’s quality. Available claims data (CD) will be analyzed to identify CD outcome variables (outcomes on patient level, e.g.: pain medication prescription after discharge) and CD quality indicators (outcomes on facility level, e.g.: proportion of patients that are prescribed pain medication after discharge), and evaluate their proximity to outcomes we obtained via primary data collection (PD outcomes; e.g.: patient-reported rating of pain).

#### Hypotheses

Using a sample of primary knee or hip replacement patients in orthopedic follow-up rehabilitation, we will test the following hypotheses:

H1a: Patient-level outcomes (outcome variables) based on claims data (CD outcome variables) show high association with patient-level outcomes as measured by a primary data quality assurance protocol currently considered best practice (PD outcome variables).

H1b: Similarly, facility-level outcomes (quality indicators) based on cross-sectoral SHI claims data (CD quality indicators) are correlated with facility-level outcomes based on the current best-practice quality assurance protocol collecting primary data (PD quality indicators).

H2: A risk-adjustment model for rehabilitation outcomes as measured by PD outcome variables improves when utilizing risk factors based on cross-sectoral SHI claims data (risk factors on patient- and facility levels) compared to a risk-adjustment model without CD risk factors.

## Study design and methods

SEQUAR combines two studies in one project: A prospective longitudinal multicenter study collecting patient- and health professional-reported data (study 1), and a retrospective cohort study using health claims data (study 2).

In study 1, patients in orthopedic follow-up rehabilitation after hip or knee arthroplasty and their physicians are repeatedly surveyed with a set of validated instruments at different phases throughout their post-op treatment. The instruments used allow comprehensive assessment of the various (long-term) outcome domains of rehabilitation (PD outcome variables), and are the current best-practice assessment against which the claims data outcomes (CD outcomes) will be tested (see section “Study outcomes”). Facility-level quality indicators based on primary data (PD quality indicators) will be calculated for individual facilities by grouped scale means.

For study 2, health claims data (CD) will be extracted from the AOK health insurance fund database (see section “Sample”). Participants of study 1 are a small subsample of the larger study 2 sample. The large study 2 sample will be used to explore, identify and validate potential CD outcome variables, CD quality indicators, and CD risk factors. The subsample of claims data from study 1 participants will be matched to the outcome variables in the PD dataset resulting from study 1, and split into two subsamples for analysis and validation, respectively. Figure 1 illustrates the data flow.

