**Fig. 1 Fig1:**
[figure not shown]
Data flow in SEQUAR

We will use the matched dataset to test our hypotheses:

For H1a, CD outcome variables should be able to serve as surrogates (proxies) for rehabilitation treatment outcomes as measured by current best-practice assessment (PD outcome variables; see outcome assessment and study design in high-quality studies on the effectiveness of multidisciplinary orthopedic rehabilitation—e.g., [28]). For H1b, we assume at least a moderate correlation (> 0.30) between CD quality indicators and PD quality indicators. To test H2, the impact of cross-sectoral CD risk factors (on patient and facility levels) on current risk-adjustment models for quality assessment will be investigated.

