### Study population and recruitment

#### Study 1: prospective longitudinal study

For study 1, ten German inpatient rehabilitation facilities (IRFs) were enlisted in the study by local representatives of the regional AOK health insurance funds, which in turn are recruiting a planned sample of 600 patients. Participating IRFs signed a collaboration agreement with the principal investigator, and each appointed a local study coordinator in charge of organization and implementation of all project tasks (e.g., recruitment of participants, distribution of patient information and consent forms, storing/safekeeping signed consent forms). Patient recruitment began in November of 2022 and will end in December 2023.

Patients eligible for participation are recruited on-site in the beginning of their orthopedic follow-up rehabilitation. Study coordinators present them with a physical copy of the study fact sheet (covering study synopsis, data protection, and other legal aspects), and ask for their participation. Those agreeing to participate sign an informed consent form. Eligibility is determined by meeting the inclusion criteria: Participants must be at least 18 years old at time of inclusion (beginning of rehabilitation), insured through AOK health insurance fund (for purposes of data availability), and receive inpatient orthopedic follow-up rehabilitation after implantation of a knee joint replacement or hip joint replacement due to osteoarthritis. Participants need to demonstrate sufficient knowledge of the German language and sufficient cognitive abilities to answer the comprehensive questionnaires independently. Patients that prematurely discontinue rehabilitation, demonstrate insufficient German or cognitive skills, or change health insurance within the study period will be excluded.

Participation in the study is incentivized with a €50 gift voucher for patients that complete all four questionnaires, while IRFs receive €120 per patient for full patient participation and completed case report forms.

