#### Study 2: retrospective cohort study

Since study 2 is exploratory in nature, no CD outcomes have yet been identified. The following steps will be taken for selection and operationalization of CD outcome variables, CD quality indicators, and CD risk factors:

A structured search for existing quality indicators, outcome variables, and risk factors of orthopedic rehabilitation will be conducted in (a) literature (e.g., Medline, Cochrane Library), (b) medical guidelines (Guidelines International Network), (c) indicator databases (e.g., [42, 43], and (d) documentation of existing procedures of quality assurance in the field of orthopedic rehabilitation. Search results will be assessed for their compatibility with claims data.The nationwide project claims database of AOK-insured patients will be analyzed to identify additional complex healthcare and rehabilitation outcomes for patients that have undergone primary knee or hip arthroplasty. This includes analysis of demographics, medical and other relevant data such as comorbidities, nursing care level, medication use, and utilization of therapeutic health service. The database will encompass data from the individual observational period for each patient, which includes the 24 months pre-surgery as well as 12 months of care after orthopedic rehabilitation. Pre-surgery data will be used as a baseline measure of study population characteristics, while the follow-up period after rehabilitation can be used to identify individual changes in relation to the baseline.Results from step (1) and (2) will be consolidated and CD outcomes and risk factors operationalized. Potential CD outcomes that represent aspects of rehabilitation treatment quality within claims data could be, for example, mobility (through provision of mobility aids), pain medication, or progression to higher nursing care levels. CD outcomes will consider care and quality aspects from all medical sectors. All quality indicators will be defined by denominators and numerators, and descriptions of inclusion, exclusion and exception criteria [44]. Denominators display a specified target population (e.g., all patients undergoing arthroplasty), whereas numerators display the number of people in the target population experiencing a specified outcome (e.g., surgical complications; [44]). These descriptive definitions can later be used to calculate individual values for rehabilitation facilities. Indicators will be translated into coded data (e.g., coded diagnoses, procedures, and prescriptions), and an appropriate reference value will be defined for each indicator.Each CD quality indicator will be adjusted for risk factors that have statistical influence on the indicator rate but cannot be influenced by IRFs. Risk factors might include patient characteristics (e.g., age, sex, comorbidity, nursing care level), or aspects of acute hospital care before rehabilitation. Relevant risk factors will be selected based on current research, results from SHI data analyses, and expert opinion [45].

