If at least two of the three validation criteria are met, the tested CD outcome variable is considered an adequate proxy for the respective PD outcome variable. Bland-Altman plots will be used for graphic evaluation of measurement differences [47, 48]. This same procedure will be applied to test H1b using CD quality indicators and PD quality indicators, which are represented by facility group mean values of PD outcome variables.

##### Hypothesis 2

H2 postulates an improvement in risk-adjustment models when considering cross-sectoral claims data, i.e., an increase in (adjusted) R^2^, and will be analyzed with nested multilevel regression models. A basic model (M0) will be estimated for each PD outcome variable using the PD confounders (see Table 2) on level 1. Models will be estimated for each time point after baseline (t1, t2, t3), and will be adjusted for *time* (rehabilitation effect) as a predictor on level 2. Furthermore, level 2 PD quality indicators will be included. Each model will be expanded with previously identified CD risk factors (on level 1 and level 2) as described in section “Study outcomes”. The nested models will be compared with Likelihood Ratio tests [49]. The analysis sample will be randomly divided into two parts, with one half allocated for analysis of risk-adjustment, and the remaining half used to validate the resulting models.

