#### Study part 2: retrospective cohort study

Data of patients who switch health insurance or decease within their individual observation period will be censored from claims data.

The claims database with be analyzed with descriptive statistics, more precisely summary statistics (measures of central tendency, spread, and dispersion), and frequency distributions. We use stratified analyses and multivariate modelling (logistic regression and generalized linear models) to estimate the influence of potential risk factors. The data structure requires multi-level regression models for cluster effects: On a patient level, we estimate the influence of case-mix variables (e.g., age, sex, comorbidity, nursing care level) on each specified outcome within a potential CD quality indicator (see section “Study outcomes”). On a facility level, we estimate the influence of quality of acute hospital care on each specified outcome within a potential CD quality indicator.

The existence of further cluster effects at IRF level will be explored. CD quality indicators will only be adjusted for risk factors an IRF has no control over, e.g., a patient’s age. Relevant measures to assess goodness-of-fit for logistic regression models are Hosmer-Lemeshow-test, Receiver Operating Characteristic (ROC Curve), Area under the curve (ROC AUC) and pseudo-R2 [50]. For general linear models, a robust estimator for estimation of covariance matrix is used.

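### H1b sets risk-adjusted claims indicators against facility means of the questionnaire scales for which no case-mix adjustment is stated; how much this distorts the comparison depends on case-mix differences the article does not quantify

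*Protocol article*

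**What the plan says.** **PD side (the reference).** The Study design and methods section gives the definition: "Facility-level quality indicators based on primary data (PD quality indicators) will be calculated for individual facilities by grouped scale means". The paragraph on testing H1b, under Data analysis and hypothesis testing, repeats it: "PD quality indicators, which are represented by facility group mean values of PD outcome variables". Neither place names adjustment for baseline status or for any confounder.

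**CD side.** The Study outcomes section for study 2 says: "Each CD quality indicator will be adjusted for risk factors that have statistical influence on the indicator rate but cannot be influenced by IRFs". The study 2 analysis section restates it: "CD quality indicators will only be adjusted for risk factors an IRF has no control over, e.g., a patient’s age".

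**Where PD confounders are used.** They enter under Hypothesis 2: "A basic model (M0) will be estimated for each PD outcome variable using the PD confounders (see Table 2) on level 1". In that model the PD quality indicators are themselves level-2 terms. No adjusted facility value is carried back to H1b.

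**How H1b is judged.** Below Figure 1: "For H1b, we assume at least a moderate correlation (> 0.30) between CD quality indicators and PD quality indicators". In the analysis section: "This same procedure will be applied to test H1b using CD quality indicators and PD quality indicators", meaning the accuracy, reproducibility and precision rules set up for H1a. The units are facilities: "ten German inpatient rehabilitation facilities (IRFs) were enlisted in the study".

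**The concern.** As written, the two sides of H1b estimate different quantities. The CD indicator aims at facility performance net of case mix. The PD indicator, as a group mean, carries performance plus whatever case mix the facility receives.

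This conflicts with the article's own reasoning. Its Background argues that patients from better hospitals probably start rehabilitation in better health, and that adjusting for earlier-sector risks should make quality assessment more accurate. The Research aims describe risk adjustment as the way to account for patient risk when a facility's quality is determined. The H1b reference leaves in the influence that the project sets out to remove.

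H1b bears on whether claims indicators can replace parts of the current survey. A valid, well-adjusted indicator can look weaker than it is, and one that has kept the facilities' case mix can look stronger.

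**Working it through.** **1. The article's own figures.** Approached: 600/0.70 = 857, stated as 860. Remaining after three post-baseline waves at 20% loss each: 600 × 0.8³ = 307, stated as 300. Both reproduce. Patients per facility: 300/10 = 30. If the split into analysis and validation halves (Study design and methods) also applies to H1b, this becomes 15. The article gives no power figure for H1b.

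**2. Model for the mismatch.** Patient-level variance is set to 1. Vq is the part due to true facility quality, Vc the part due to between-facility case mix, Ve = 1 − Vq − Vc the remainder, and m the patients per facility. The CD indicator is taken to measure quality perfectly, case mix is independent of quality, and adjustment removes all case mix without noise.

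- Correlation with unadjusted PD means: √[Vq / (Vq + Vc + Ve/m)]
- Correlation with adjusted PD means: √[Vq / (Vq + Ve/m)]
- A fully unadjusted, noise-free CD indicator (quality plus the same case mix) against unadjusted PD means: √[(Vq + Vc) / (Vq + Vc + Ve/m)]

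Vq = 0.03 and all values of Vc are assumptions; the documents supply neither.

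**3. Results at m = 30.**

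| Vc | Perfect CD vs unadjusted PD | Perfect CD vs adjusted PD | Unadjusted CD vs unadjusted PD |
|---|---|---|---|
| 0.005 | √(0.03/0.0672) = 0.67 | 0.69 | 0.72 |
| 0.01 | √(0.03/0.0720) = 0.65 | 0.70 | 0.75 |
| 0.03 | √(0.03/0.0913) = 0.57 | 0.70 | 0.81 |
| 0.06 | √(0.03/0.1203) = 0.50 | 0.71 | 0.86 |

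The loss is about 0.03 to 0.05 for small case-mix differences and about 0.13 to 0.21 for large ones. In every row the unadjusted CD indicator beats the perfect one, so the ordering of good and bad indicators can reverse. That comparator is an extreme case.

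At m = 15 with Vc = 0.03 to 0.06, the perfect indicator reaches 0.49 to 0.45, against about 0.57 with adjusted means.

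**4. Against the 0.30 benchmark.** Let s = Vc/(Vq + Vc), the case-mix share of systematic between-facility variance. Leaving sampling noise aside, observed r = true r × √(1 − s).

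- s = 0.25 (Vc = 0.01 above): a true 0.30 appears as 0.30 × √0.75 = 0.26; showing 0.30 needs a true 0.30/√0.75 = 0.35.
- s = 0.50 (Vc = 0.03 above): a true 0.30 appears as 0.30 × √0.50 = 0.21; showing 0.30 needs a true 0.30/√0.50 = 0.42.

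If case mix correlates −0.3 or +0.3 with quality, a true 0.50 at s = 0.50 appears as 0.30 or 0.40, against 0.35 under independence.

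**5. Ten facilities.** In a simulation with 30 patients in each of ten facilities, a quality intraclass correlation of 0.05 and a true correlation of 0.70 (both assumed), the chance that the sample correlation exceeds 0.30 is 0.83 at s = 0, 0.77 at s = 0.25 and 0.69 at s = 0.50. By Fisher's z, an observed 0.30 on ten units has a 95% interval of tanh(0.310 ± 1.96/√7), or −0.41 to 0.78.

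**The case against.** **The full plan may adjust the means.** The article never calls them raw or unadjusted; its wording could describe only the level of aggregation, and it refers elsewhere to existing risk-adjustment models. This is possible. But the article defines the indicator twice as a group mean and states twice that the CD indicator is adjusted. The asymmetry is in the text.

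**Baseline may be partly handled.** A reader might infer that the PD indicator ignores t0 status altogether. The article does not support that: it does not say whether follow-up levels or changes from t0 are averaged. Change scores would deal with baseline in part. This point stands.

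**The size is assumed, and the population is narrow.** Patients have joint replacement for osteoarthritis, inpatient follow-up rehabilitation and one insurer group, so case mix may vary little. If it accounts for 0.5 to 1% of variance, the loss is only 0.03 to 0.05. This also stands.

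**Rejection of valid indicators is not shown.** A reader might infer that H1b will turn down good indicators. In all the scenarios calculated, a perfect indicator stays above 0.30. The three carried-over rules do not all move one way either: with case mix independent of quality, extra PD variance widens the regression intervals and enlarges the PD standard deviation, which makes the accuracy and precision rules easier to meet. Ten units remain the larger source of uncertainty.

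**A modelled reference may change the question.** H1b asks whether claims indicators track the existing survey procedure. That is a fair reason to keep the unadjusted comparison visible, but not to have it as the only one.

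**Conclusion.** The concern holds in conditional form. On the article's own definitions, H1b compares an adjusted quantity with one for which no case-mix adjustment is stated, against its own rationale for risk adjustment. Where case mix differs between the ten facilities, agreement with a valid adjusted CD indicator is diluted and an indicator sharing that case mix is favoured.

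The asymmetry needs no assumption; its size does. The correlations in the working rest on an assumed 3% quality variance, case mix independent of quality and perfect adjustment. Within that frame the effect runs from minor to material, and the documents do not show where in the range this study lies. They do not support a flat statement that the distortion is large or that valid indicators will fail. With ten facilities, case-mix distortion could not be told apart from poor proxy performance after the fact, which is a reason to settle the definition beforehand.

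**What to change.** In the Study design and methods definition and in the H1b paragraph, define the reference as a case-mix-adjusted facility value: the mean observed-minus-expected score, or the facility effect, from a separate patient-level model. That model should contain the t0 value of the outcome and those Table 2 confounders measured at t0 that lie outside the facility's control, the principle already used for the CD indicators. State whether follow-up levels or change scores are analysed.

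The H2 basic model as written cannot supply this value: it already includes the PD quality indicators at level 2, so the derivation would be circular.

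Report the H1b comparison with unadjusted group means alongside as a sensitivity analysis, which also keeps the link to the existing procedure.

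**Cost.** No new data are needed, since the t0 outcomes and confounders are already collected. One further model must be specified and fitted on about 300 patients, or about 150 if the sample is halved. Coefficients estimated from ten facilities add some noise to the reference. The change does not remove the imprecision of a facility-level comparison on ten units.
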